### Sample size

2.13

The trial obeys the principle of a superiority design. Combined pilot cases observation and experts’ opinion [35,36], it is estimated that the primary outcome, diarrhoea severity score on day 28, can differ by 3 points between the probiotics or placebo groups, with a standard deviation of 6.8. Given an *α* = 0.05 and a *β* = 0.20, the sample size is calculated to be at least 81 per group. After considering the drop-out rate (20% or lower), the sample size should be 97 or more per group. The final sample size is determined to be 100 per group with a total of 200 cases.

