### Statistical analysis

2.15

The following four datasets will be used for the analysis [1]: the data of all volunteers who completed the follow-up and [2] the data of three subgroups divided according to compliance (≥80%, 60–80%, and <60%), which will be analysed to validate the robustness of the analysis results. The following analysis methods will be used to analyse each dataset.

First, to analyse the inter-group differences in each outcome measure, Z test (as the sample size is quite more than 10, using Z test instead of Wilcoxon signed-rank sum test) will be used for the outcome measures, including the diarrhoea severity score, weekly mean frequency of defecation, weekly mean stool appearance score, weekly mean stool urgency score, and emotional state score, at each observation point. In the analyses, the *P*-value indicating statistical significance will be set at 0.05. More detailed information about how to analyse and present inter-group differences is clearly provided in Table 2.

**Table 2 tbl2:** The format to analyse and present the inter-group differences between probiotic and placebo groups at each observation point.

Groups	P5	P25	Median	P75	P95	Z value	*P*
*L. plantarum* p9							
Placebo							

Note: The data applied here includes the diarrhoea severity score, weekly mean frequency of defecation, weekly mean stool appearance score, weekly mean stool urgency score, and emotional state score; P5, P25, P75, P95 means the 5th, 25th, 75th, 95th percentile, respectively; Z = |T-n1*(N+1)/2–0.5|/SQRT [n1*n2(N+1)/12], n1 refers to the smaller sample size between the two compared groups, while n2 refers to the sample size of the other group; N = n1+n2; T is calculated using method of Wilcoxon signed-rank sum test.

Then, to identify the intra-group changing trends with the consecutive phases, namely, pre-, during and post-probiotic administrating, the *Kruskal-Wallis* rank sum test will be used for multiple comparisons of the diarrhoea severity score, weekly mean frequency of defecation, weekly mean stool appearance score, weekly mean stool urgency score, and emotional state score for each group, i.e., probiotic group or placebo group. In the analyses, the *P*-value indicating statistical significance will be adjusted to be 0.05/[k(k-1)/2], where k is the number of sample groups in the comparison. More detailed information about how to analyse and present inter-group differences is clearly provided in Table 3.

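### The drop-out allowance is computed as 81 × 1.2 = 97 where 81/0.8 = 102 per group is needed; the chosen 100 per group keeps 81 completers only up to 19% drop-out, a minor shortfall

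*Protocol article*

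**What the plan says.** Section 2.13 of the protocol article (Sample size) assumes that the day-28 diarrhoea severity score "can differ by 3 points between the probiotics or placebo groups", "with a standard deviation of 6.8". "Given an *α* = 0.05 and a *β* = 0.20", it concludes that "the sample size is calculated to be at least 81 per group". It then makes the drop-out allowance: "After considering the drop-out rate (20% or lower), the sample size should be 97 or more per group". It ends by rounding up: "The final sample size is determined to be 100 per group with a total of 200 cases".

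Section 2.15 (Statistical analysis) lists four datasets. The overall one is "the data of all volunteers who completed the follow-up"; the other three are subgroups by compliance.

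**The concern.** The plan gives 20% as the highest drop-out rate to be covered and 81 as the number needed per group. The number to enrol should then still leave 81 after one in five is lost. 97 does not, and neither does 100.

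The allowance matters here because the overall dataset in section 2.15 consists of completers. Each drop-out reduces the number analysed, and none of the listed datasets brings the lost volunteers back. A reader of section 2.13 would take 100 per group as three above the minimum, when it is two below the correct one. What is at stake is an accurate statement of how much drop-out the trial can absorb, which readers will need if the result is null.

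**Working it through.** **Inputs, all from section 2.13 unless noted.** Difference 3; SD 6.8; α = 0.05; power 0.80 (β = 0.20); equal groups; 81 evaluable per group; drop-out at most 20%. Completers-only overall dataset: section 2.15. Whether the test is one- or two-sided is not stated ("The trial obeys the principle of a superiority design" does not settle it). Two-sided is inferred below because it reproduces 81.

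**Step 1. Reproduce 81.** Normal approximation for two means:

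n = 2 × [6.8 × (1.960 + 0.842)/3]² = 80.65, so 81 per group. This matches the plan. The one-sided version gives 63.5, so 64, and does not match.

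**Step 2. Reproduce 97.**

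- n × (1 + d) = 81 × 1.20 = 97.2. This matches the stated 97 after rounding down.
- n/(1 − d) = 81/0.80 = 101.25, so 102. This does not match.

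The plan therefore used the first form. The second is the one that leaves 81 after a 20% loss.

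**Step 3. What each enrolled number delivers.** The largest tolerable drop-out is 1 − 81/n. Power is Φ[(3/6.8) × √(m/2) − 1.96], where m is the number of completers per group.

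| Enrolled per group | Completers at 20% drop-out | Largest drop-out that keeps 81 | Power at 20% drop-out |
|---|---|---|---|
| 97 | 77.6 | 16.5% | 78.5% |
| 100 | 80 | 19.0% | 79.7% |
| 102 | 81.6 | 20.6% | 80.5% |

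For 100 per group: (3/6.8) × √40 − 1.96 = 2.790 − 1.960 = 0.830, and Φ(0.830) = 79.7%. With the full 81 completers the same formula gives 80.2%.

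**Step 4. How far the power figures can be trusted.** Section 2.8 (Primary outcome) defines the score as the sum of three means, each scored 0 to 3, so it runs from 0 to 9. The largest SD possible on that range is about 9/2 = 4.5, reached when half the values are 0 and half are 9. An SD of 6.8 is out of reach. The powers in Step 3 therefore follow from the plan's inputs and do not forecast the trial's actual power. Steps 2 and 3 on numbers retained use only 81 and 20%, so that arithmetic stands whatever happens to the SD.

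**The case against.** The strongest reply is that the trial never planned to stop at 97. It enrols 100 per group, and the text treats 20% as a ceiling. For every drop-out rate up to 19% the 100 retains 81. At exactly 20% it is one completer short per group, about 0.3 percentage points under 80% power. On the unrounded requirement, 80.65/0.8 = 100.8, so 100 is only one per group short. All of this stands, and it is why the point is minor. It does not remove the error: a ceiling of 20% is what the allowance has to cover, and neither 97 nor 100 covers it.

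A reader might infer that the trial loses its stated 80% power across the whole drop-out range. The documents do not support that, since at 100 per group the shortfall arises only above 19%. The 78.5% for 97 per group describes a number that the plan rounds up from.

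A reader might also want to enlarge the shortfall by arguing that a t-test, or the rank-based Z test planned in section 2.15, needs more volunteers than the normal approximation. The approximation is a conventional way to reach 81, and the planned test is not a t-test. The efficiency usually quoted for a rank test holds for normal data, whereas this outcome is a bounded composite of ordinal scores, for which a rank test may be less or more efficient. The documents give no basis for a figure.

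Finally, it can be said that restating a power near 80% would lend precision to an SD that the score cannot produce. That is fair, and any restated power should carry the condition.

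**Conclusion.** The figure of 97 is wrong as written: at 20% drop-out, 81 completers require 102 per group. The chosen 100 per group falls short by one completer per group at exactly 20% and is sufficient up to 19%. By the plan's own normal approximation this is 79.7% power against a target of 80%.

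This rests on the stated 81 and 20%, on drop-outs being absent from the overall dataset as section 2.15 has it, and, for power only, on two-sided testing and the inputs 3 and 6.8. It is a minor correction to a number. It is not evidence that the trial is materially underpowered, and the unattainable SD means that the documents cannot show a real power loss in either direction.

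**What to change.** In section 2.13, replace the minimum of 97 with 102 per group at 20% drop-out. Add that the chosen 100 per group retains 81 evaluable volunteers at up to 19% drop-out and 80 at 20%. Keep enrolment at 200.

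If power is restated, use one method throughout (the normal approximation that gives 81 also gives 79.7% for 80 completers), and mark it as conditional on a difference of 3 and an SD of 6.8. Those inputs should be reconciled with the 0–9 score in section 2.8 before any power figure is relied on.

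The drop-out correction costs a sentence or two, with no change to enrolment, design or analysis. The stated margin becomes slightly less favourable: 100 moves from three above the quoted minimum to two below the correct one.

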### Data collection and monitoring

2.14

An independent data management team (DMT) is formed to periodically assess the study quality and safety. Volunteers are required to complete the defecation diary (Appendix 2) daily online and the DASS-21 (Appendix 3) online as scheduled in Table 1, both of which are promptly downloaded and collected by the data analysts. The data of demographic profiles, defecation diary (Appendix 2) and DASS-21 (Appendix 3) completed online by volunteers can downloaded as excel spreadsheets for further analysis. For gut microbiome and metabolomics test, volunteers have to prepare stool samples as the instructions of test kit at home, at day 0 (observing period of pre-administrating), 28 (observing period of administrating) and 42 (observing period of pro-administrating), all of which are timely collected, separately stored and sent for detection at −80 °C in a special stool storage kit from Guangdong longsee company (www.longseemed.com). The data of gut microbiome and metabolomics detected from stool samples will detected by Key Laboratory of Dairy Biotechnology and Engineering, Ministry of Education.

All the data will be submitted to the DMT for managing and monitoring. The DMT will promptly check the data and urge the data collectors to resolve it when uncertainty about the data occurs. All records that contain names, ID Number, or other personal identifiers (e.g., informed consent forms), are stored separately from study records. The database will be password protected by the DMT. The team also has the authority to carry out an interim analysis or terminate the next-step study according to the following situations [1]: if the probiotics does not present effect on gut microbiome, then the study will not further conduct the detections of faecal metabolome [3]; if any severe adverse events related to probiotics occurs, DMT will suggest terminating the study.

### Statistical analysis

2.15

The following four datasets will be used for the analysis [1]: the data of all volunteers who completed the follow-up and [2] the data of three subgroups divided according to compliance (≥80%, 60–80%, and <60%), which will be analysed to validate the robustness of the analysis results. The following analysis methods will be used to analyse each dataset.

First, to analyse the inter-group differences in each outcome measure, Z test (as the sample size is quite more than 10, using Z test instead of Wilcoxon signed-rank sum test) will be used for the outcome measures, including the diarrhoea severity score, weekly mean frequency of defecation, weekly mean stool appearance score, weekly mean stool urgency score, and emotional state score, at each observation point. In the analyses, the *P*-value indicating statistical significance will be set at 0.05. More detailed information about how to analyse and present inter-group differences is clearly provided in Table 2.

**Table 2 tbl2:** The format to analyse and present the inter-group differences between probiotic and placebo groups at each observation point.

Groups	P5	P25	Median	P75	P95	Z value	*P*
*L. plantarum* p9							
Placebo							

Note: The data applied here includes the diarrhoea severity score, weekly mean frequency of defecation, weekly mean stool appearance score, weekly mean stool urgency score, and emotional state score; P5, P25, P75, P95 means the 5th, 25th, 75th, 95th percentile, respectively; Z = |T-n1*(N+1)/2–0.5|/SQRT [n1*n2(N+1)/12], n1 refers to the smaller sample size between the two compared groups, while n2 refers to the sample size of the other group; N = n1+n2; T is calculated using method of Wilcoxon signed-rank sum test.

Then, to identify the intra-group changing trends with the consecutive phases, namely, pre-, during and post-probiotic administrating, the *Kruskal-Wallis* rank sum test will be used for multiple comparisons of the diarrhoea severity score, weekly mean frequency of defecation, weekly mean stool appearance score, weekly mean stool urgency score, and emotional state score for each group, i.e., probiotic group or placebo group. In the analyses, the *P*-value indicating statistical significance will be adjusted to be 0.05/[k(k-1)/2], where k is the number of sample groups in the comparison. More detailed information about how to analyse and present inter-group differences is clearly provided in Table 3.

**Table 3 tbl3:** The format to analyse and present the intra-group differences among the four observation points in a probiotic or placebo group.

Groups	P5	P25	Median	P75	P95	H value	*P*
Day 0							
Day 14							
Day 28							
Day 42							

Note: The data here includes the diarrhoea severity score, weekly mean frequency of defecation, weekly mean stool appearance score, weekly mean stool urgency score, and emotional state score; P5, P25, P75, P95 means the 5th, 25th, 75th, 95th percentile, respectively; H is calculated using method of *Kruskal-Wallis* rank sum test.

In addition, the statistical analyses of metagenomics and metabolomics will be performed using the R software (v.4.0.2) and Adobe Illustrator. PCA and PLS-DA analysis will be performed and visualized using the R package vegan, ggplot and ggpubr, and the adonis *P*-value will be generated based on 999 permutations. *t*-test, *Wilcoxon* test and *Kruskal-Wallis* test will be used to evaluate differences in various variables between and within groups; *P* values will be corrected for multiple testing using the Benjamini-Hochberg procedure. Meanwhile, Pearson and spearman correlations will be used to analyse the correlations between different indicators in clinical, metagenomics and metabolomics.

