### Primary outcome

2.8

The primary outcome is the diarrhoea severity score, which is set as to the gastrointestinal symptom rating scale (GSRS) [[33], [34], [35], [36]]. The outcome measure is equal to the sum of mean defecation frequency score per day, mean stool consistency score per time, and mean stool urgency score per time within the past 7 days (see Appendix 2). The diarrhoea severity score will be assessed on days 0 (baseline), 14, 28, and 42. A higher score indicates more severe diarrhoea, Table 1. The details of calculation are as follows.

A defecation diary developed with reference to the literatures [33,34,37] will be completed daily online by the volunteers (Appendix 2). Based on the diary, the mean defecation frequency score per day, mean stool consistency score per time, and mean stool urgency score per time will be obtained. The defecation frequency score is ranked as: 0-point, one to two a day; 1-point, three to four times a day; 2-point, five to six times a day; 3-point, seven times a day or more frequently. The mean defecation frequency score per day is equal to “total defecation frequency score within the past 7 days/7”. The stool appearance score refers to Bristol stool type (Appendix 1) and must be recorded for each defecation: types 4–7 correspond to 0–3 points, respectively. The mean stool consistency score per time is equal to “total stool consistency scores within the past 7 days/total times”. The stool urgency score must be also recorded for each defecation: 0-point, no urgency; 1-point, a little urgency; 2-point, sudden need to have a defecation that must be addressed immediately; or 3-point, incontinence resulting in uncontrolled defecation and may stain pants. The mean stool urgency score per time is equal to “total stool urgency score within the past 7 days/total times”.

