### Compliance monitoring and withdrawn

2.12

The L. *plantarum* P9 and placebo powder are supplied as treatment packs and packaged in boxes. At the beginning of administration phase, the probiotics or placebo packaging boxes enough for 28-day intervention are distributed to corresponding volunteers. Volunteers are required to keep all the used (empty) and unused treatment packs which are collected to check whether a volunteer takes the probiotics or placebo as the study's schedule. Based on the number of empty packs, the compliance rate is calculated for individual volunteer. A compliance rate ≥80% indicates a good compliance. To improve compliance, a WeChat group is established for the cohort of volunteers, and the study personnel can post messages via the WeChat group, reminding volunteers to take the samples as scheduled and complete the defecation diary (Appendix 2). In addition, each volunteer can receive 300 RMB as a reward once they complete the follow-up.

Volunteers can withdraw from the trial for the following reasons [1]: Persistent adverse reactions (cannot be resolved after taking certain measures) possibly involving the four kinds of AEs listed in “Safety evaluation part” [2,39] Volunteers can autonomously withdraw from the study at any time for any reason.

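### All four planned analysis datasets are defined by events after randomisation, so selective loss can bias the primary comparison and the compliance subgroups cannot serve as its robustness check

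*Protocol article*

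**What the plan says.** Section 2.15 of the protocol article opens with a closed count: "The following four datasets will be used for the analysis". They are "the data of all volunteers who completed the follow-up and [2] the data of three subgroups divided according to compliance". In full, the last three are "the data of three subgroups divided according to compliance (≥80%, 60–80%, and <60%), which will be analysed to validate the robustness of the analysis results". It then adds "The following analysis methods will be used to analyse each dataset", so the between-arm rank test and the within-arm test are run in all four.

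Three other places bear on who ends up in these sets:

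- Section 2.12 lists persistent adverse reactions as a reason for withdrawal and adds "Volunteers can autonomously withdraw from the study at any time for any reason". It also defines compliance from the count of empty packs returned.
- Section 2.13 fixes the primary time point as day 28 and allows for loss: "After considering the drop-out rate (20% or lower), the sample size should be 97 or more per group".
- Table 1 runs follow-up to day 42, two weeks after the primary time point.

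**The concern.** Randomisation makes the arms comparable at day 0. Any set chosen by later events keeps that comparability only if those events are unrelated to outcome in the same way in both arms. Completion may not meet that condition, because adverse reactions to the allocated powder are a listed route out of the trial and a volunteer whose diarrhoea does not improve is free to leave. If such losses are heavier or more selective in one arm, the completers in that arm look better than the arm as randomised. The opposite pattern could hide a real effect.

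The wording also discards usable data. Read literally, a volunteer who has a day-28 score but leaves before day 42 has not completed follow-up and drops out of the day-28 primary comparison.

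The safeguard offered is the split by compliance. Compliance is observed after randomisation as well, so comparing arms within a compliance band compares people who sorted themselves into that band, possibly for different reasons in each arm. Agreement or disagreement between the bands and the completer result says little about whether the completer result is sound.

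**Working it through.** **Inputs from the article.** 100 per group; planned difference 3 points; SD 6.8; α = 0.05; power 80%; drop-out up to 20% (all section 2.13). The test is the rank-sum Z with continuity correction (Table 2).

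**The plan's own figure.** n per group = 2 × [6.8 × (1.96 + 0.842) / 3]² = 80.65, rounded up to 81. This matches the article with a two-sided test. The planned effect is 3 / 6.8 = 0.44 SD. At 20% drop-out, up to 0.20 × 200 = 40 randomised volunteers fall outside the completer set.

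**Why SD units are used below.** The score in section 2.8 sums three components of 0 to 3, so it runs from 0 to 9 and its SD cannot exceed 4.5. An SD of 6.8 does not fit that scale, so results in points would mislead.

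**Selective loss, assumed scenario.** No true effect; normal scores; 100 randomised per arm; the same fraction q lost in each arm. In one arm loss is decided by a variable with correlation ρ to the day-28 score. In the other it is random. The expected shift in the completer mean is ρ × φ(z₁₋q) / (1 − q).

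- q = 20%: φ(0.842)/0.80 = 0.350, giving 0.10, 0.17 and 0.35 SD for ρ = 0.3, 0.5 and 1.
- q = 10%: φ(1.282)/0.90 = 0.195, giving 0.06, 0.10 and 0.19 SD.
- q = 5%: φ(1.645)/0.95 = 0.109, giving 0.03, 0.05 and 0.11 SD.

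Simulating the Table 2 test (20,000 trials per cell, nominal two-sided 5%) gives these error rates:

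| Loss per arm | ρ = 0.3 | ρ = 0.5 | ρ = 1 (exactly the worst scorers leave) |
|---|---|---|---|
| 5% | about 6% | about 7% | about 10% |
| 10% | about 7% | about 10% | about 23% |
| 20% | about 10% | about 20% | about 58% |

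With ρ = 0 the rate stays at about 5%, as it should.

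A second parameterisation agrees in scale. If those lost in one arm differ from its completers by 0.25, 0.5 or 1 SD, 20% loss shifts the completer mean by 0.20 times that, i.e. 0.05, 0.10 or 0.20 SD. The error rate of a test of means is then about 6%, 10% or 24%.

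**The compliance split.** Again assume no true effect, 70% of each arm in the top band, and compliance related to outcome in one arm only. With an SD of 6.8, simulation gave a spurious difference of −1.5 to −2.4 points in the top band and +3.5 to +5.5 points in the rest, for correlations of about 0.45 and 0.71. Divided by 6.8, that is roughly −0.22 to −0.35 SD and +0.51 to +0.81 SD. The bands err in opposite directions although nothing is there.

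They are also small. If 80 completers per arm split 70/20/10% (assumed), the bands hold 56, 16 and 8 per arm, with power for the planned effect of about 65%, 24% and 14%.

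**The case against.** The sponsor can fairly say that completers are still analysed in the arm they were assigned to. A reader might infer from the dataset list that the randomised comparison is given up altogether. The text does not support that: the comparison is weakened by possible selection, and if loss is light or unrelated to outcome the bias is small.

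A reader might also infer that anyone who stops the powder is removed. The criterion is completing follow-up, not treatment. Someone who stops the packs but keeps the diary stays in, and the lowest compliance band allows for such people. Nor does the article say outright that the compliance bands are drawn only from completers, though that is the natural reading. The objection to them holds either way.

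It is tempting to say that selective loss could manufacture an effect as large as the planned one. In these scenarios it does not: the most extreme gives 0.35 SD against 0.44 SD, about 80% of it, and needs a perfect link between loss and score in one arm and none in the other.

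The divisor in the frequency component, "total defecation frequency score within the past 7 days/7", might be read as scoring an unrecorded diary day as zero. The article states no rule for unrecorded days, and one may sit in an analysis plan not shown, so nothing here rests on it.

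Finally, analysis-set details often sit in an analysis plan. That would answer a silence, but this article is not silent: it gives a closed list of four. A plan that follows the list carries the fault, and one that departs from it contradicts the article.

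**Conclusion.** The point stands as a defect in the stated analysis sets. All four depend on post-randomisation events, none is stated to contain everyone randomised, and the planned robustness check shares the weakness it is meant to test.

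The bias is possible, not certain, and the documents give no data on who drops out or why. At the 20% ceiling, with selection in one arm only, a moderate link between loss and outcome (0.3 to 0.5) raises the nominal 5% error rate to about 10% to 20%. At 10% loss it is about 7% to 10%. The 58% figure (23% at 10% loss) is a ceiling, not an expectation. If selection were alike in both arms, the bias under no effect would largely cancel. Because this concerns the primary comparison of a superiority trial and is cheap to correct, it should be changed before the data are analysed.

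**What to change.** - Define the primary dataset as all randomised volunteers in their assigned group, whatever their compliance or completion.
- Use every observed score, including the day-28 scores of volunteers who leave before day 42.
- State a method for missing day-28 scores and add one missing-not-at-random sensitivity analysis, such as a tipping point. The choice of primary test can remain the sponsor's; this point does not require replacing the rank test with another model.
- Keep the completer analysis and the analysis of volunteers with at least 80% compliance as supportive only, and report the two lower compliance bands descriptively.
- Remove the statement that the compliance subgroups validate robustness.

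The cost is revised wording and a little analysis work. Scores up to withdrawal should be available from the daily online diary. The article describes no collection after withdrawal, and 174 volunteers were already enrolled when it was written (section 4), so scores missing after withdrawal will have to be modelled, not retrieved.

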### Study interventions

2.6

One probiotics or placebo powder pack per day. One probiotics powder pack contains 100 billion colony-forming units (CFU) of *L. plantarum* P9. *L. plantarum* P9 powder comprises *L. plantarum* P9 (40%), maltodextrin (20%), orange powder (20%), and maltitol (20%). The placebo comprises maltodextrin (60%), orange powder (20%), and maltitol (20%) and has the same appearance, packaging, and taste as the *L. plantarum* P9 powder. Both probiotics and placebo packs are stored in a 4 °C, dry place away from direct sunlight. At the end of the phase, all unused probiotics or placebo and used (empty) packs are collected, so as to calculate volunteers’ compliance.

The study is designed to include three phases, a period of screening (an observation period of pre-administrating), an observation period of administrating, and an observation period of post-administrating (Table 1). The interventions in each phase are as follows.(1)Period of screening (observation period of pre-administrating) (days −14 to 0): volunteers do not receive probiotics or placebo. Eligibility screening are performed as described in “volunteer recruitment part” (Table 1).(2)Observation period of administrating (days 0–28): 1) For probiotics group: volunteers take *L. plantarum* P9 powder with warm boiled water (below 40 °C) on a full stomach, 1 pack per day (i.e., 100 CFU/d); if volunteers have to take antibiotics during the administration, the probiotics is taken 2 h later. 2) For placebo group: volunteers take the placebo in the same manner as probiotics group.(3)Observation period of post-administrating (days 29–42): No interventions are taken during the study.

**Table 1 tbl1:** Study and follow up schedule.

Item		Period of screening (observation period of pre-administrating)		Observation period of administrating		Observation period of post-administrating
		Visit 0	Visit 1	Visit 2	Visit 3	Visit 4
		(Days −14 to −1)	Day 0	Day 14	Day 28	Day 42
Collection of volunteers' basic information		**✓**				
Screening		**✓**				
Informed consent form		**✓**				
Stool test (including occult blood)		**✓**				
Defecation diary		Completed Online Daily				
Primary outcomes	Diarrhoea severity score		**✓**	**✓**	**✓**	**✓**
Secondary outcomes	Weekly mean frequency of defecation		**✓**	**✓**	**✓**	**✓**
	Weekly mean stool appearance score		**✓**	**✓**	**✓**	**✓**
	Weekly mean stool urgency score		**✓**	**✓**	**✓**	**✓**
	Emotional state score		**✓**	**✓**	**✓**	**✓**

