Collectively, the study protocol will provide high-quality evidence for the use of probiotics as a diarrhoea agent when it is strictly conducted out, providing evidence regarding whether and to what extent *L. plantarum* p9 can improve the defecation and well-being of individuals with chronic diarrhoea. If the study findings are as expected, *L. plantarum* p9, taken as probiotics, may become an optimal nonmedical intervention option for patients with chronic diarrhoea.

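### The between-group analysis leaves the collected day-0 score unused and plans no between-group estimate or confidence interval, which costs efficiency and interpretability but does not bias the test

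*Protocol article*

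**What the plan says.** Section 2.15 of the protocol article states that "to analyse the inter-group differences in each outcome measure, Z test" will be applied to five clinical scores, separately at each observation point. The formula in the note to Table 2 is the large-sample two-sample rank-sum statistic on raw scores (the note calls it signed-rank, but the formula is for two independent groups). It contains no covariate and no change from day 0.

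Table 2 fixes the between-group output: five percentiles for each arm, then Z and P. It has no column for a between-group difference or a confidence interval.

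Table 1 lists "Diarrhoea severity score" as the primary outcome, recorded at days 0, 14, 28 and 42, and section 2.8 labels day 0 as baseline. Day 0 otherwise appears only as one of the visits tested and as one row of the within-arm Kruskal-Wallis layout in Table 3.

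The Discussion describes the trial as "providing evidence regarding whether and to what extent" the probiotic improves defecation and well-being. Section 2.13 sizes it on the assumption that the "diarrhoea severity score on day 28, can differ by 3 points between the probiotics or placebo groups", "with a standard deviation of 6.8".

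**The concern.** Two things are given up. First, a baseline value of the primary score, measured with the same diary, is in hand and does not inform the treatment comparison. If it correlates at all with the day-28 score, adjusting for it removes outcome variance that the planned test leaves in, including the part due to chance differences between arms at day 0.

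Second, the trial is sized on a 3-point difference, yet no planned output estimates that difference with a measure of uncertainty. A reader would learn whether P is below 0.05 and could see the two distributions, but would not learn how large an effect the data support or exclude. A non-significant result would be especially hard to read, since no interval would show whether a 3-point benefit had been ruled out.

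**Working it through.** **Inputs from the article.** Difference 3, SD 6.8, α = 0.05, power 80%, 100 per group, drop-out up to 20% (section 2.13). Scoring rules from section 2.8. **Input not given:** the correlation r between the day-0 and day-28 scores, assumed here to be 0.2, 0.3, 0.5 or 0.7.

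**1. Reproduce the plan's figure.** The plan states: "Given an *α* = 0.05 and a *β* = 0.20, the sample size is calculated to be at least 81 per group". Two-sided, unadjusted: n = 2 × [6.8 × (1.960 + 0.842)/3]² = 80.65, rounded up to 81. One-sided gives 64 and does not match. The sample size is therefore a two-sided, unadjusted comparison of means that takes no credit for baseline.

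**2. Completers.** With 100 per group and 20% drop-out, 100 × 0.8 = 80 per group.

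**3. Relative gain, which does not depend on the SD.** Adjustment multiplies the residual variance by (1 − r²), so the effective sample size is n/(1 − r²).

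| Assumed r | 1/(1 − r²) | 80 completers per group act like |
|---|---|---|
| 0.2 | 1.04 | 83 |
| 0.3 | 1.10 | 88 |
| 0.5 | 1.33 | 107 |
| 0.7 | 1.96 | 157 |

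**4. Power on the protocol's own figures (illustrative).** Standardised effect 3/6.8 = 0.441, 80 per group, two-sided t-test: 79.2%. Replacing 0.441 by 0.441/√(1 − r²) gives:

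- r = 0.2: 80.8%
- r = 0.3: 82.8%
- r = 0.5: 89.3%
- r = 0.7: 97.3%

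The planned test is a rank-sum, not a t-test. In a simulation with normal data (4,000 trials per r, 80 per arm), the rank-sum test had 76–78% power whatever r was. ANCOVA had 79%, 83%, 88% and 97% at r = 0, 0.3, 0.5 and 0.7.

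**5. Why step 4 is only illustrative.** Section 2.8 sums a mean frequency score, a mean consistency score and a mean urgency score. Each is scored 0–3, so the total lies between 0 and 9. The largest SD possible on that range is half of it, 9/2 = 4.5, so 6.8 cannot occur. At SD 4.5 with a 3-point difference and 80 per group, unadjusted t-test power is already 98.7%, and r = 0.5 raises it only to 99.8%.

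**6. What an interval would show.** On the protocol's SD, the half-width of a 95% CI for the difference is 1.96 × 6.8 × √(1 − r²) × √(2/80). That is about 2.1 points at r = 0, 2.0 at r = 0.3, 1.8 at r = 0.5 and 1.5 at r = 0.7. These widths carry the same caveat as step 4. Table 2 as laid out would report no such quantity.

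**The case against.** **The test is sound as it stands.** A reader might infer that ignoring day 0 biases the result, or that a chance imbalance at baseline invalidates it. The documents do not support that. Allocation is by computer-generated random sequence (section 2.5), and the type I error of an unadjusted test already allows for chance imbalance. The sample size also never relied on adjustment. This objection stands, and it limits the point to efficiency and interpretability.

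**Table 2 is not bare.** It is tempting to say that the plan reports nothing about the size of effect. It does report medians and other percentiles for each arm, and Table 3 repeats them by visit, so a crude difference in medians can be read off. That much stands. A subtraction of medians has no stated precision, however, and is not the quantity that the rank-sum test addresses.

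**The gain may be small.** A reader might infer from the broad entry rule (loose stools on at least a quarter of occasions, section 2.2) that baseline must predict day 28 well, and so expect power to rise from 79% to 97%. The entry rule says nothing about how stable a 7-day diary score is over four weeks, and the article gives no correlation. At r = 0.2 the gain is 4% in effective sample size. The absolute power figures also rest on an SD that the score cannot have.

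**A rank method is defensible, and covariates may be left to an analysis plan.** For a score bounded at zero a rank test is a reasonable choice, and the fix below allows for that. The second part carries less weight: the article states the test, its formula and the layout of its output, so this is a choice made in the document rather than detail left open.

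**Conclusion.** The point holds in a limited form. As written, the between-group comparison makes no use of the collected day-0 score and produces no between-group estimate or confidence interval, so the extent of benefit is not answered with any stated precision. This is a worthwhile improvement, not an error that undermines the trial.

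The missing estimate and interval follow directly from Table 2 and rest on no assumption. The efficiency gain is 1/(1 − r²): its direction is certain for any non-zero r, it is nil at r = 0, and its size (roughly 4% to 96% more effective sample size across r = 0.2 to 0.7) is assumption. No claim about absolute power should be drawn from it until the SD is reconciled with the 0–9 scale.

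**What to change.** By a dated amendment made before any unblinding, including unblinding for an interim analysis, which section 2.5 permits:

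1. Analyse the day-28 diarrhoea severity score with the day-0 score as covariate (ANCOVA, or rank ANCOVA if a rank method is preferred for a bounded score). Report the adjusted between-group difference with its 95% CI.
2. Keep the rank-sum test alongside it, with a Hodges-Lehmann difference and 95% CI.
3. Add difference and 95% CI columns to Table 2.
4. Treat the other four scores in the same way.

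The cost is analysis wording and table columns; the day-0 data are already collected. The downsides are a mild model assumption, which the rank-based result checks, and an amendment late in enrolment: the Trial status section reports 174 volunteers enrolled of the 200 planned. The amendment should record that it was made without knowledge of allocation.
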